#### Evaluation of the intervention

To measure the client satisfaction after the intervention, the 8-item Client Satisfaction Questionnaire (CSQ-8) [48] is used. All items are scored on a 4-point scale ranging from 1 to 4. For each individual a ‘satisfaction-score’ is computed by averaging their scores on the 8 items. Also a question is included about how the participants evaluated the intervention on a scale from 1 to 10. Furthermore, the participants are asked (1) the amount of hours they have on average spend completing the intervention; (2) to what extent they have completed the exercises; (3) if they have used the different components of the web-based intervention; and (4) if they were satisfied with the received feedback. We also asked them to write down three aspects of the intervention they appreciated most and three things they appreciated least. Finally we asked them if they have suggestions for improvement of the intervention.

#### Economic evaluation

The economic evaluation will be carried out using the Trimbos questionnaire for Costs associated with psychiatric illness (Tic-P) [49] and the Productivity and Disease Questionnaire (PRODISQ) [50]. Healthcare consumption is measured with two items of the Tic-P. The items are (1) in how far have participants made use of the healthcare facilities in the last four weeks? and (2) to what extent did they receive other help (e.g. from family and friends or homecare) in the last four weeks?. Participants can answer these questions with yes (1) or no (0). In case they made use of a healthcare facility (answer ‘yes’), they are asked how often they made use of it. Production losses due to illness and absenteeism will be measured with 6 items of the PRODISQ. Utilities will be derived from the EuroQol (EQ-5D) scores. Mean incremental cost per patient and the incremental cost utility ratio (ICER) will be calculated. The economic evaluation will be assessed from a societal perspective, thus including the intervention costs (such as costs for building the intervention, costs for hosting the website), the costs of formal and informal health care (TIC-P), and the economic costs due to productivity losses in paid and unpaid work in the four weeks preceding the trial (PRODISQ).

### Statistical analysis

The data of partners will be coded directly after being collected and will be entered into a statistical database to ensure accuracy and completeness of the data. Before we start with our data analysis, we will check if our data is normally distributed. If it is not, we will choose an non-parametric test. All data will be analyzed using SPSS version 20.

#### Descriptive statistics

A flow chart of participation during the total study will be drawn. Reasons for drop-out will be summarized. Percentages of missing values and dropout will be displayed. Background variables and summarized scores on questionnaires as mentioned in chapter 6 will be given. Basic psychometric analyses will be conducted to verify scale structure and internal consistency of the used questionnaires.

#### Effects

One-way ANOVA’s and χ^2^-tests will be performed to see if there are no significant differences at baseline between the two conditions for any of the demographic variables or outcome measures. Non-significant differences will indicate successful randomization. Intention-to-treat analyses will be conducted with use of SPSS missing values analysis to impute all missing data on the continuous measuring multiple imputation methods in SPSS. To examine differences between the conditions on all outcome measures, ANOVA (group x time) will be used. In the case of significant group x time – interactions, Tukey’s post hoc tests will be used.

Effect sizes on the primary outcome variable (HADS total) at post-intervention will be calculated with Cohen’s D using the means and pooled standard deviations of the measurements of the conditions (effect size of above .56 are considered large, .33-.55 are considered moderate, and less than .33 are considered as small [51].

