### Randomization

Respondents who are eligible, have provided their informed consent, and have completed the baseline (T0) questionnaire, are automatically randomized and divided over the three conditions. Randomization is stratified for gender, so an equal distribution of female and male participants in all conditions is warranted. Additionally we stratify for the perceived stage of disease, which is measured by the following item: (1) My partner is still in treatment and we have good hope that he/she will recover; (2) The treatment is completed and we are moving on with our lives; (3) My partner is unlikely to be cured. All participants receive an e-mail with the outcome of randomization and a link to start the intervention. Participants are informed about the three different conditions. They know that there is a waiting list control condition and that there are two experimental versions, one with automatic feedback and another with personal feedback. Participants in the experimental conditions will receive immediate access to the web-based intervention *Hold on, for each other*. The intervention is individually administered and the participants can access the intervention at any time, from any place, free of charge. Participants that will be placed on a waiting list have the opportunity to access treatment as usual (TAU) and they will be referred to relevant websites such as the website of Dutch Cancer Society (http://www.kwfkankerbestrijding.nl/ or http://www.kanker.nl) for information. Three months after the baseline measurement, which is directly after the first follow-up measurement at three months, participants on the waiting list receive the opportunity to follow the web-based intervention *Hold on, for each other* with automated feedback. They will also be invited to fill out measurements 6 and 12 months after the baseline measurement (see flowchart, Figure 1).

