#### Socio-demographics and disease-related characteristics

The following socio-demographics of the partners are assessed: sex, age, education, marital status, cultural background, children, work status. Regarding their partner’s disease, participants are asked about type of cancer, time since diagnosis, current treatment and self-reported stage of disease (see description in paragraph ‘Randomization’).

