#### Outcome measures

*Psychological distress*—the primary outcome—is measured with the total Hospital Anxiety and Depression Scale (HADS) [25]. The HADS is a 14-item questionnaire that measures the presence and severity of anxiety and depressive symptoms. Answering categories range from 0 to 3 and the items are added to a scale score that can range from 0 – 42. Higher scores mean more symptoms of psychological distress.

*Mental health* is assessed with the Mental health Continuum – Short Form (MHC-SF) [30,31]. The MHC-SF is a 14-item questionnaire that measures three dimension of positive mental health [30]: emotional well-being (3 items), psychological well-being (6 items), and social well-being (5 items). Participants are asked to rate the frequency of feelings they have experienced in the past month. Items are scored on a 6-point scale ranging from 1 to 6. A mean score is computed ranging from 1 to 6 with higher scores indicating higher levels of positive mental health. The Dutch version of the MHC-SF has shown good psychometric properties [31].

*Caregiver strain* is assessed with the 13-item Caregiver Strain Index (CSI) [32]. The CSI contains at least one item to measure burden in each of the following major domains: employment, financial, physical, social and time. Each item can be answered with ‘yes’ (1) or ‘no’ (0). A CSI score is computed by counting the number of ‘yes’, resulting in a score from 0-13. The CSI has shown good psychometric properties [32].

*General health* of the partners of cancer patients is assessed with one item of the RAND 36 [33,34]. This item “How would you rate your own general health?” can be answered on a 5-point scale ranging from 1 - 5, with higher scores indicating better general health.

*Health-related quality of life* of the participants is measured with the EuroQol EQ-5D [35]. The EQ-5D is a validated instrument for measuring health-related quality of life and it covers five domains of health: mobility, self-care, usual activity, pain/discomfort and depression/anxiety. Each of the five domains has three severity levels; 0 (none), 1 (some), and 2 (severe).

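### Non-significant baseline tests are taken as proof that randomisation succeeded, a criterion that shows neither sound allocation nor balance between the arms

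*Protocol article*

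**What the plan says.** In the Effects section of the Protocol article, ANOVAs and chi-square tests are to be run at baseline "to see if there are no significant differences at baseline between the two conditions for any of the demographic variables or outcome measures". The next sentence gives the reading of the result: "Non-significant differences will indicate successful randomization". The section states no significance level for these tests, no allowance for their number, and no step to follow a significant one. The planned outcome comparison is a group by time ANOVA.

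The Randomization section says that eligible participants who have given consent and completed the T0 questionnaire "are automatically randomized and divided over the three conditions". Allocation is stratified by gender and by perceived stage of disease. The trial has three conditions, so the reference to two in the Effects section is a slip.

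**The concern.** A baseline significance test asks whether the arms were drawn from the same population. Under random allocation the answer is known: they were. Here the baseline answers are also given before allocation, so they cannot be influenced by it. A small p-value is then a chance result, and a large one adds nothing to what the procedure already guarantees. Whether randomisation was sound is judged from how the sequence was generated, concealed and applied.

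If successful is meant as balanced, the criterion fails for another reason. A p-value depends on sample size as well as on the size of the imbalance and takes no account of how strongly the variable predicts outcome. A difference in a strong predictor could be passed over because p>0.05.

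At stake is the trial report's statement about its own validity. That statement would rest on a test unable to support it in either direction.

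**Working it through.** **Inputs from the Protocol article**
- Demographic variables: 7 ("sex, age, education, marital status, cultural background, children, work status", in Socio-demographics and disease-related characteristics).
- Outcome measures: 5 (HADS total, MHC-SF, CSI, the RAND 36 general health item and EQ-5D, in Outcome measures).
- Arms: 3 (Study design).
- Size per arm at T0: 87 (Sample size calculation).
- Alpha: 0.05 two-sided, stated only for the sample size. Its use in the baseline tests is an assumption.

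**Step 1. The plan's own figure.** For d = 0.5, two-sided alpha 0.05 and power 0.80, the exact t calculation gives 64 per arm (power 0.801). Then 64 + 5 = 69, 69 / 0.80 = 86.25, rounded up to 87, and 3 × 87 = 261. The stated sizes are reproduced.

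**Step 2. How large an imbalance stays non-significant?** One-way ANOVA with 3 arms of 87 has 2 and 261 − 3 = 258 degrees of freedom. The 5% critical value is F = 3.03. Let g be the observed gap in units of the within-arm SD.
- Two arms g apart, third midway: the squared deviations sum to g²/2, so F = (87 × g²/2)/2 = 21.75 g². Setting this to 3.03 gives g = √(3.03/21.75) = 0.37.
- One arm g away from the other two: the squared deviations sum to 2g²/3, so F = (87 × 2g²/3)/2 = 29 g², and g = √(3.03/29) = 0.32.

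Against the d = 0.5 for which the trial is powered, these gaps are 0.37/0.5 = 74% and 0.32/0.5 = 64%.

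**Step 3. How often would a correctly randomised trial show at least one significant difference?** For k independent tests at 0.05 the chance is 1 − 0.95^k.

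| Tests counted | k | Chance |
|---|---|---|
| 7 demographic + 5 outcome | 12 | 46.0% |
| Same, without sex (stratified, so hardly able to differ) | 11 | 43.1% |
| Same, also without EQ-5D (its row in Table 4 shows no time points as extracted) | 10 | 40.1% |

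**Step 4. Allowing for correlation.** The five outcome measures come from the same person and will be correlated. The article gives no correlations, so values from 0 to 0.7 were assumed. A simulation of 3 arms of 87 under simple randomisation (3,000 trials per setting, one continuous demographic, the other demographics independent three-category variables) gave 42-45% for 12 tests and 38-43% for 11. The Monte Carlo standard error is about √(0.42 × 0.58/3000) = 0.9 percentage points. Correlation lowers the figure somewhat.

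**The case against.** The strongest reply is that the text says less than a critic may read into it. It says that non-significance indicates success. It does not say that significance indicates failure, and it attaches no exclusion, covariate selection or change of model to a significant result. The group by time ANOVA is planned whatever the baseline tests show. All of this stands. A reader might infer that the plan will declare failure in about half of sound trials, or will choose covariates after seeing the data. The article does not say so; the 40-46% applies only if the unstated converse is used.

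A reader might also add the 4 disease-related variables and reach 1 − 0.95^16 = 56%. The sentence names only demographic variables and outcome measures, and Table 4 lists the disease-related variables in a separate row, so that figure is not supported.

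It can also be said that a large baseline difference could expose a fault in the automated system, so the tests are not wholly without information. That is fair, but it makes them at best a weak alarm. It does not make a quiet alarm evidence of success, which is what the sentence asserts.

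The mention of two conditions is a separate wording error. It adds nothing to the argument about the tests.

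Finally, a condensed article may leave covariates to a fuller plan. Their absence is therefore not a fault here. The stated criterion is, because it is written out and wrong as written.

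**Conclusion.** The point holds against the criterion as stated. Non-significant baseline tests indicate neither sound allocation nor balance: with 87 per arm, an observed gap of up to about 0.37 SD between two arms (third midway), or 0.32 SD for one arm against the other two, passes unnoticed. Applied in reverse, the rule would be met by chance in roughly 40-46% of correctly randomised trials. That range assumes alpha 0.05 and the 7 plus 5 named variables. It falls to about 38% with sex left out and a correlation of 0.7 among outcomes.

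The harm is to how validity is judged and reported. A reader might infer that the primary comparison is itself compromised. It is not directly so, since no estimate or test in the article is made to depend on the baseline results. The point should be corrected, but it does not undermine the design.

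**What to change.** 1. Delete the baseline significance tests and the sentence that interprets them.
2. Describe baseline characteristics by arm (means and SDs, or counts and percentages) for all three conditions, and correct the reference to two. Judge randomisation from the allocation procedure.
3. Adjust the outcome analysis for the baseline score of the outcome, gender and perceived stage of disease, fixed in advance whatever the observed balance. Because the group by time ANOVA already carries baseline as a time level, the clean form is to model the follow-up scores with the baseline score as covariate and the two stratification factors as terms.

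Items 1 and 2 are wording. Item 3 is a small change to the analysis model. All three covariates are already collected before randomisation, so data collection, sample size and trial conduct stay as they are.

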## Methods/Design

### Study design

This study is a prospective randomized controlled trial with three parallel groups:Experimental condition 1: Web-based intervention *Hold on, for each other*, with personal support.Experimental condition 2: Web-based intervention *Hold on, for each other*, with automated support.Waiting list control condition: Participants will be on a waiting list for 3 months from entry/intake. They will receive Hold on, for each other (with automated feedback) after the first follow-up measurement, three months after the start of the intervention for the experimental condition.

This study has been approved by the Twente Medical Ethics Committee under the file number P13-17 (Dutch trial register: NTR4035). Participation is voluntary and all respondents will provide written informed consent before inclusion.

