### Sample size calculation

Based upon a previous, similar study [54] we expect effect sizes of at least d = 0.5. To demonstrate the presence of an effect of at least d = 0.5 as statistically significant in a two-tailed test at alpha = 0.05 and a power of (1-beta) = 0.80, a minimum of 64 participants in each condition will be required at follow-up (power calculation in G*Power). We have extended our sample size with 5 participants per condition in order to take normal distribution of the data as well as possible post hoc tests into account. Anticipating a drop-out rate of 20% between T0-measurement and T3-measurement, at least 87 participants per condition need to be included at T0-measurement. The total study cohort comprises thus 261 participants.

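### The gated group-by-time F and Tukey rule gives no single decision under the planned multiple imputation unless a pooled test is named; pooled baseline-adjusted T1 contrasts would give one, with more precision

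*Protocol article*

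**What the plan says.** The trial has three arms: personal support, automated support and a waiting list (Study design). The primary outcome, psychological distress, "is measured with the total Hospital Anxiety and Depression Scale (HADS"), total score (Outcome measures).

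The section Effects sets out the analysis in consecutive sentences:

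- Missing data: "Intention-to-treat analyses will be conducted with use of SPSS missing values analysis to impute all missing data" on the continuous measures, by "multiple imputation methods in SPSS".
- Test: "To examine differences between the conditions on all outcome measures, ANOVA (group x time) will be used".
- Gate: "In the case of significant group x time – interactions, Tukey’s post hoc tests will be used".

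The section Sample size calculation gives a two-sided alpha of 0.05, 87 participants per condition at T0, and the expected loss: "Anticipating a drop-out rate of 20% between T0-measurement and T3-measurement". The article gives no number of imputations, no imputation model, and no way of combining the F test, the gate or the Tukey tests across imputed data sets.

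**The concern.** Multiple imputation produces several completed data sets. The usual combining rule takes an estimate and its standard error from each one. The article's decision rule is instead an omnibus F with two or more numerator degrees of freedom, a yes/no gate, and then studentised-range tests. Applied data set by data set, it gives several F values and several gate decisions, and these can differ.

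Two things are at stake. If the data sets disagree and no pooled test has been fixed, the wording does not say what the primary conclusion is. And if an analyst settled the matter by reading the F from one completed data set, imputed scores would count as observed, the error term would be too small, and the false-positive rate would exceed the stated 0.05.

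**Working it through.** **1. The article's own figures.** A two-sample t test with d = 0.5, two-sided alpha 0.05 and power 0.80 needs 63.77, so 64 per arm. Adding 5 gives 69; 69/0.80 = 86.25, so 87; and 3 × 87 = 261. The stated sample size reproduces.

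**2. Set-up.** From the article: three arms of 87, alpha 0.05, 20% drop-out. Assumed, because the article does not give them: correlation ρ = 0.5 to 0.7 between baseline and follow-up HADS, equal variances (set to 1), a proportion p of follow-up scores missing completely at random, imputation by regression on arm and baseline, and an analysis of T0 and one follow-up. With two time points the group-by-time F equals a one-way ANOVA on change, with 2 and 3 × 87 − 3 = 258 degrees of freedom and a 5% critical value of 3.031.

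**3. F read from one completed data set, closed form.** Per arm:

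- Variance the ANOVA assumes for the mean change: 2(1 − ρ)/n.
- Actual variance: (1 − ρ²)/[n(1 − p)] + (1 − ρ)²/n, plus p(1 − ρ²)/[n(1 − p)] from the random imputation draw.
- Ratio: R = [(1 + ρ)(1 + p)/(1 − p) + (1 − ρ)]/2.

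At p = 0.20 and ρ = 0.6, R = (1.6 × 1.5 + 0.4)/2 = 1.40. The true error is then about P(F > 3.031/1.40) = P(F > 2.165). For 2 and 258 degrees of freedom this is (1 + 2 × 2.165/258)^(−129) = 0.117.

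| Missing | R (ρ = 0.5 / 0.7) | Closed-form error | Simulated, one data set | Simulated, pooled F |
|---|---|---|---|---|
| 10% | 1.167 / 1.189 | 0.076 / 0.080 | 0.080 / 0.082 | 0.052 / 0.052 |
| 20% | 1.375 / 1.425 | 0.112 / 0.121 | 0.117 / 0.120 | 0.054 / 0.052 |
| 30% | 1.643 / 1.729 | 0.160 / 0.175 | 0.159 / 0.171 | 0.052 / 0.049 |

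The simulated columns come from 8000 null trials per setting with 20 imputations. The pooled F is the Li-Raghunathan-Rubin D1 test. The two routes agree.

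**4. Disagreement at the gate.** In the same null trials, the 20 separate F tests did not all fall on the same side of p = 0.05 in 34% (ρ = 0.5) to 36% (ρ = 0.7) of trials at 20% missing, and in 17% to 20% at 10% missing. This shows how often the rule has no single answer if each F is read separately. It does not describe a pooled analysis.

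**5. What the adjusted contrast gains.** Variance of one arm-versus-waiting-list contrast at p = 0.20 and ρ = 0.6 (observed n = 69.6 per arm), ignoring the small extra variance from a finite number of imputations:

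- Baseline-adjusted: 2 × 0.64/69.6 = 0.01839, SE 0.1356.
- Unadjusted change: 0.01839 + 2 × 0.16/87 = 0.02207, SE 0.1486.

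The ratio is 0.01839/0.02207 = 0.83. At d = 0.3 the standardised effects are 0.3/0.1356 = 2.21 and 0.3/0.1486 = 2.02. Power per contrast at two-sided 0.05 is therefore about 60% and 52%, before any multiplicity adjustment. Simulation gave about 59% and 51%. Under no effect, the adjusted contrast pooled over imputations rejected in 5.2% of simulated trials (ρ = 0.6, 20% missing, 5 imputations).

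**The case against.** The strongest reply is that nothing here is stated wrongly. Multiple imputation and an omnibus test can be combined: D1 gives one F, one p-value and one gate decision at about the nominal level, and pairwise contrasts can be pooled and then adjusted. The number of imputations and the pooling rule are details that an article commonly leaves to the full protocol or analysis plan, which is not shown. This stands. The missing pooling rule is not in itself a defect, and any claim that the two methods cannot be used together would be false.

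A reader might also infer that the trial will take its primary F from a single filled-in data set, perhaps because the imputation sentence names both a missing values analysis and multiple imputation. The article does not support this. The sentence is clumsy but reads as a tool followed by a method, no second imputation method is named, and the commitment is to multiple imputation. The error rates in the single-data-set column therefore measure a risk, not the plan.

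The 20% is also loss over twelve months to T3. If fewer scores are missing at T1, the inflation is nearer the 10% row.

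What survives is narrower. The article does fix a gated decision rule, and that rule yields one decision under its own missing-data method only through a pooled test it does not name. A simpler rule is available that pools directly and is more precise.

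**Conclusion.** The concern holds in limited form. As worded, the primary decision rule has a single outcome only if a pooled interaction test is used. Such a test exists and would hold the error rate at about 0.05, so the planned analysis is not shown to be invalid. If the F were read from one completed data set, type I error would be about 0.11 to 0.12 at 20% missing and about 0.08 at 10%. These sizes rest on the assumed correlation, on missingness completely at random and on an analysis of T0 and one follow-up. Even with correct pooling, the group-by-time contrast is less precise than a baseline-adjusted one, whose variance is about 17% lower at ρ = 0.6 and 20% missing. The change is worth making.

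**What to change.** For the primary outcome, replace the gated F and Tukey rule with the two arm-versus-waiting-list contrasts on HADS total at T1, the last measurement before the waiting list is offered the intervention. Estimate them from a linear model with arm, baseline HADS, gender and perceived disease stage, the last two being the randomisation strata. Fit the model in each imputed data set, pool coefficients and standard errors by Rubin's rules, and adjust the two p-values for multiplicity. State the number of imputations (at least 20 is reasonable) and an imputation model that includes arm, strata, baseline and the other visits. A likelihood-based mixed model on the observed data, without imputation, is an acceptable alternative.

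If the full analysis plan already specifies pooling of the interaction test and the post hoc comparisons, the sponsor need only confirm it to settle the question of a single decision; the gain in precision would still favour the change.

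The cost is analysis wording and slightly more analysis work, with no new data or participants. The p-values will be less favourable than those from a single completed data set.

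### The primary HADS effect is tested as a difference in change but sized and labelled from post-intervention scores that ignore baseline; one baseline-adjusted T1 estimate would be more precise and would match its test

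*Protocol article*

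**What the plan says.** All references are to the protocol article.

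- **Primary outcome** (Outcome measures): psychological distress "is measured with the total Hospital Anxiety and Depression Scale (HADS"), collected in every arm at T0 and T1 (Table 4).
- **Test** (Effects): "To examine differences between the conditions on all outcome measures, ANOVA (group x time) will be used". Post hoc comparisons follow only conditionally: "In the case of significant group x time" interactions, by Tukey's method.
- **Effect size** (Effects): "Effect sizes on the primary outcome variable (HADS total) at post-intervention will be calculated" as Cohen's d, "using the means and pooled standard deviations of the measurements of the conditions". No baseline term or change score is mentioned.
- **Labels** (Effects): "effect size of above .56 are considered large, .33-.55 are considered moderate, and less than .33 are considered as small".
- **Baseline differences** (Effects): checked for significance only, with the statement "Non-significant differences will indicate successful randomization". No adjustment follows.
- **Stratification** (Randomization): gender and perceived stage of disease, not baseline HADS.
- **Planning value** (Sample size calculation): "To demonstrate the presence of an effect of at least d = 0.5 as statistically significant".

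**The concern.** A group x time interaction compares arms on change from baseline. A Cohen's d from follow-up means compares arms on where they ended. The first subtracts the whole baseline difference and the second subtracts none of it, so the p-value and the graded effect size rest on different contrasts of the same data.

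The graded d is the number readers will set beside the planning value of 0.5. If the arms happen to differ on HADS at T0, the article could report a significant interaction with a small effect, or a non-significant interaction with a moderate one, and nothing in the plan says which to believe. Baseline HADS is collected in everyone, and leaving it out of d also gives up precision.

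**Working it through.** **1. The plan's own figure.** A two-sided two-sample t-test with d = 0.5, alpha 0.05 and power 0.80 needs 63.8, so 64 per arm. Then (64 + 5)/0.80 = 86.25, so 87 per arm, and 3 x 87 = 261. The sample size reproduces. The checks below use 69 per arm, the number the plan expects at follow-up.

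**2. The gap between the two quantities.** In SD units, with equal SDs at both times:

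(difference at follow-up) - (difference in change) = baseline difference, b.

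This is an identity and needs no assumed correlation. By chance alone SE(b) = sqrt(2/69) = 0.170, with a 95% range of +/-0.33. The probability that b exceeds 0.2 in either direction is that of |z| > 0.2/0.170 = 1.17, about 24%.

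**3. Where b goes.** The article gives no correlation r between baseline and follow-up HADS, so r is an assumption. For a given b, the post-score d shifts on average by r x b and the change contrast by -(1 - r) x b. With a true d of 0.5 and b = 0.25:

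| r | post-score d | change contrast |
|---|---|---|
| 0.5 | 0.5 +/- 0.125 = 0.625 or 0.375 | 0.375 or 0.625 |
| 0.7 | 0.5 +/- 0.175 = 0.675 or 0.325 | 0.425 or 0.575 |

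The first value in each cell is for b in one direction, the second for the other. A difference of this size lies inside the 95% chance range and can move the label.

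**4. Precision.** Simulation of two arms and two time points (normal scores, equal SDs, 69 per arm, true d = 0.5, 20,000 trials per setting) gave:

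| estimator | mean | SD, r = 0.4 | SD, r = 0.5 | SD, r = 0.7 |
|---|---|---|---|---|
| post-score d | 0.50 | 0.17 | 0.17 | 0.17 |
| change / pooled SD | 0.50 | 0.19 | 0.17 | 0.135 |
| baseline-adjusted d | 0.50 | 0.16 | 0.15 | 0.13 |

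All three are centred on the truth. The adjusted estimate is the most precise at every r. The change contrast is noisier than the post-score at r = 0.4 and equal to it at r = 0.5.

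**5. Labels.** At a true d of 0.5 the correct label is moderate. A normal approximation for the post-score d (SD 0.17) gives P(d < 0.33) = P(z < -1.00) = 0.16 and P(d > 0.56) = P(z > 0.35) = 0.36. Together that is 52%, against 52-53% in simulation. After adjustment the simulated rate is 50% (r = 0.4) to 41% (r = 0.7). The post-score and adjusted labels differ from each other in 20% to 36% of trials.

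**6. Disagreement with the test.** With the Tukey threshold for three groups, a non-significant change comparison accompanies a post-score d of at least 0.33 in 26% (r = 0.4) to 5% (r = 0.7) of trials. A significant one accompanies a d below 0.33 in 5% to 13%.

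These rates need a comparator. The Tukey threshold corresponds to d = 0.40, above the 0.33 cut-off. Testing the post-score itself would therefore still give moderate but not significant whenever d falls between 0.33 and 0.40: P(-1.00 < z < -0.59) = 0.28 - 0.16 = 12%. Only part of the 26% comes from mixing two quantities, and at r = 0.7 the mixed rate (5%) is below the matched one.

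**The case against.** **The plan does not define two different effects.** A reader might infer that the test and the d target different treatment effects, or that the post-score d is biased. Randomisation rules this out: both have the same expectation, and all estimators average 0.50 in simulation. This objection stands.

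**The post-score d is not the only imperfect quantity.** It absorbs only a share r of the baseline difference, while the change contrast over-corrects by 1 - r. At r = 0.4 the change contrast is the weaker of the two. It would be wrong to say that d carries the whole imbalance and the test carries none. This stands as well.

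**Contradictory headlines cannot be put down purely to baseline imbalance.** The 12% comparator shows this. Most of the mislabelling is also ordinary sampling error around narrow bands, and adjustment removes only about 3 to 12 percentage points of it.

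**The unadjusted d suits its context.** The sample size is a two-group comparison at d = 0.5, a d from reported means is a common descriptive figure, and no decision is tied to the labels. This lowers the stakes. It does not explain why the labelled estimate should ignore a baseline measure already in hand.

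**The article is condensed.** It does not say which time points enter the ANOVA, so the calculation is a simplified two-arm, two-time-point version. But the test, the formula and the cut-offs are all stated in the text, and none of them adjusts for baseline.

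**Conclusion.** The point holds as one of precision and coherence. The labelled effect size and the primary test use baseline HADS in different ways, and in any one trial they differ by a chance amount with a standard error of about 0.17 SD. That is large beside label bands about 0.23 wide (0.33 to 0.56). Adjustment for baseline would reduce the SD of d from about 0.17 to 0.16-0.13, cut mislabelling at d = 0.5 from about 53% to 50-41%, and let the estimate and its p-value come from one model.

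The size of the chance gap rests only on 69 per arm and equal SDs. The gains rest on an assumed correlation of 0.4 to 0.7 and on normal scores. They are modest at the low end and useful at the high end. The documents do not support calling the reported d biased, the sample size wrong or the result invalid.

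**What to change.** In the Effects section:

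- Estimate each comparison with the waiting list as the between-arm difference in HADS total at T1, adjusted for baseline HADS (ANCOVA, or a mixed model with baseline as covariate).
- Use that same model for the primary T1 test. A group x time ANOVA does not yield a baseline-adjusted difference, so changing the formula for d alone would leave d and p in different models.
- Divide the adjusted difference by the pooled SD of the raw HADS scores, stating whether T0 or T1, and report a 95% CI.
- Apply the .33/.56 labels to that figure and show the raw post-score d beside it.

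**Cost:** a short change to the text and no new data, since HADS is collected at T0 and T1 in all arms. The primary T1 comparison moves from the group x time ANOVA to the adjusted model, and d can no longer be recomputed from the table of raw means alone. Showing the raw d alongside covers that second loss.
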